### Overview of implementation component of trial

#### Intervention sites

An OCHIN team member identified 99 clinics in 32 eligible health center organizations within OCHIN. Of those invited, 23 clinics in 7 health center organizations agreed to participate (23 % of eligible clinics) and 76 clinics in 25 organizations declined (77 % of eligible clinics). The 7 participating organizations are located in 3 Medicaid expansion states (Oregon, California, and Ohio). These organizations varied in size; the number of primary care clinic sites per organization ranged from 1 to 6. Due to the possible correlation among clinic sites in the same organization, an independent biostatistician randomized the 23 clinics by service organization. A covariate-constrained cluster randomization [44] was used to balance the number of clinics between the two treatment arms. The randomization was balanced using the following covariates: state the organization was located in (Oregon vs. non-Oregon), total number of patients per organization, and percentage of uninsured patients per organization. The biostatistician and research team members were blind to the clinics during randomization. Once randomized, the study team was given the list of clinics participating in each study arm (11 in Arm I and 12 in Arm II).

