**Methods/design:**

This study uses a hybrid cluster-randomized design—a combined effectiveness and implementation trial—in community health centers (CHCs) in the USA. Eligible CHC clinic sites will be randomly assigned to one of two groups in the trial’s implementation component: tools + basic training (Arm I) and tools + enhanced training + facilitation (Arm II). A propensity score-matched control group of clinics will be selected to assess the tools’ effectiveness. Quantitative analyses of the tools’ impact will use electronic health record and Medicaid data to assess effectiveness. Qualitative data will be collected to evaluate the implementation process, understand how the HIT tools are being used, and identify facilitators and barriers to their implementation and use.

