## Methods/design

### Trial design

This is a two-arm, cluster-randomized trial with an external matched control group of clinics, which utilizes a hybrid design: an effectiveness and implementation trial [32, 36–38]. To test for *implementing the tools*, intervention clinics will be randomized to one of the two implementation support arms (see Fig. 1). Thus, all intervention clinics will receive the health insurance support HIT tools but will be randomly assigned to Arm I (tool + basic training) or Arm II (tools + enhanced training + facilitation) as depicted in Fig. 1. The *implementation* component of the trial will evaluate the relative impact of the different support strategies in Arm II. For the *effectiveness* component of the trial, we will compare the intervention group (all participating clinics) to a propensity score-matched [39–41] group of control clinics to assess the extent to which the use of insurance support HIT tools facilitates continuous health insurance coverage and improved cancer prevention care.

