### Analytic strategy

#### Quantitative analysis of the effectiveness component of the trial

We will estimate pre- and post-implementation rates of insurance coverage and cancer screenings for clinics in the intervention group and the matched control group. For each patient in the study population, we will determine continuity of coverage and receipt of age- and gender-appropriate recommended cancer screening and preventive care 18 months pre- and 18 months post-intervention. The intervention group will be compared with the matched control group using a difference-in-differences (DID) approach. We will utilize generalized linear/non-linear mixed models, which offer flexible regression modeling to accommodate different sources of correlations (serial and intra-clinic), categorical and continuous covariates, and fixed and time-dependent covariates. This general model allows us to study a wide range of dependent variables, including logistic regression (binary data), beta regression (percent data), Poisson regression (count data), and Gaussian regression (normally distributed data). For example, we will use a random-effect logistic regression model to analyze insurance continuity at pre- and post-intervention periods (dependent variables) as a function of whether a patient belongs to a control or intervention CHC (primary independent variable) and other possible confounders. Serial and intra-clinic correlations will be modeled as random effects.

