#### Quantitative analysis of the implementation component of the trial

Similar to the effectiveness aspect of the trial, we will compare the pre- and post-intervention rates of patients’ insurance coverage and receipt of recommended cancer screenings using DID generalized linear/non-linear mixed models comparing Arm I and Arm II. Moreover, post-implementation, we will assess and compare use of the tools across the study arms, including information such as who uses which tools and functions, as well as frequency and timing of use. This will help identify individual- and clinic-level factors associated with more frequent use of the health insurance support HIT tools.

To evaluate tool use, we will assess monthly data (e.g., percent of patient charts with evidence of tool use) in regression models to estimate associations between use and patient panel characteristics. Additionally, we will describe and compare the characteristics of patient encounters with tool use vs. those with no tool use, via random-effect logistic regression models that assess associations between use of the insurance support HIT tools (dependent variables) and socio-demographic characteristics (independent variables) and other possible confounders.

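### Seven whole organizations were randomised because their clinics are correlated, but the stated models carry only serial and intra-clinic correlation, so Arm I vs Arm II is in effect tested on 23 independent clinics

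*Protocol article*

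**What the plan says.** The Intervention sites section reports that "23 clinics in 7 health center organizations agreed to participate", and that "the number of primary care clinic sites per organization ranged from 1 to 6". On allocation it says: "Due to the possible correlation among clinic sites in the same organization, an independent biostatistician randomized the 23 clinics by service organization". The balancing covariates are the organization's state, its total number of patients and its percentage of uninsured patients. The result was 11 clinics in Arm I and 12 in Arm II; the number of organizations per arm is not stated.

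Elsewhere the clinic is described as what was randomised. The abstract has "Eligible CHC clinic sites will be randomly assigned to one of two groups", and the Trial design section has "intervention clinics will be randomized to one of the two implementation support arms".

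The section on quantitative analysis of the effectiveness component names serial and intra-clinic correlation as the sources its mixed models accommodate, and then states: "Serial and intra-clinic correlations will be modeled as random effects". The section on the implementation component says it proceeds in a similar way, "using DID generalized linear/non-linear mixed models comparing Arm I and Arm II". Neither section mentions organization.

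**The concern.** In a cluster-randomised comparison, the analysis must allow for variation between the units that were allocated. Here those units are organizations, yet the highest level in the stated model is the clinic. All clinics of one organization share an arm. If their changes over time move together, for example through shared enrolment practice or local outreach, they supply less information than the same number of independent clinics.

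The difference-in-differences form removes stable differences between organizations. It does not remove differences between organizations in the amount of change. A separate pre-to-post change for each clinic would not help either, because it treats the changes of sister clinics as independent.

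Arm I versus Arm II is the trial's only randomised comparison. Chance differences between a handful of organizations could be reported as an effect of facilitation. The effectiveness comparison is exposed too, because its intervention clinics sit in the same 7 organizations.

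**Working it through.** **Inputs from the article (Intervention sites).** 7 organizations; 23 clinics; 1 to 6 clinics per organization; 11 and 12 clinics per arm. The recruitment counts agree: 23/99 = 23.2%, 76/99 = 76.8%, 23 + 76 = 99 clinics, 7 + 25 = 32 organizations, 11 + 12 = 23. Because 7 and 25 add up to exactly 32, no organization was split between taking part and declining.

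**Assumptions.** The article gives no alpha, no intraclass correlation and no organization sizes beyond the range. I take a two-sided 5% test. Let ρ be the share of the between-clinic variance in pre-to-post change that lies between organizations, varied from 0 to 0.5. I assume 3 organizations in one arm and 4 in the other.

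**Size sets.** There are 19 sets of 7 sizes with smallest 1, largest 6 and total 23 that can be split 11/12. Of these, 18 allow a 3-versus-4 split of organizations.

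**Variance of the arm difference.** With organization sizes m, and total between-clinic variance set to 1:

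- ignoring organization: 1/11 + 1/12 = 0.1742
- true: ρ × (Σm²/11² + Σm²/12²) + (1 − ρ) × 0.1742, each sum taken over the organizations in that arm

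Example: sizes 1, 4, 6 against 2, 3, 3, 4.

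- Σm²/11² = (1 + 16 + 36)/121 = 0.4380
- Σm²/12² = (4 + 9 + 9 + 16)/144 = 0.2639
- sum = 0.7019
- at ρ = 0.20: (0.20 × 0.7019 + 0.80 × 0.1742)/0.1742 = 1.61
- at ρ = 0.50: (0.50 × 0.7019 + 0.50 × 0.1742)/0.1742 = 2.51

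Over the 18 sets the understatement factor is 1.15–1.19 at ρ = 0.05, 1.59–1.74 at 0.20 and 2.47–2.85 at 0.50.

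**Degrees of freedom.** With clinics as units, 23 − 2 = 21, critical t = 2.080. With organizations as units, 7 − 2 = 5, critical t = 2.571. The ratio 2.571/2.080 = 1.24 makes intervals 24% wider before any variance correction.

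**False-positive rate with no arm effect.** Clinic-level changes were simulated 5,000 times per cell, using one 11/12 split for each of the 18 sets. The figures are medians, with the range over sets in brackets.

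| ρ | Clinic-level t-test, 21 df | Same test, normal critical value | Organization-mean t-test, 5 df |
|---|---|---|---|
| 0 | 5.0% (4.5–5.6) | 6.4% | 4.0% |
| 0.05 | 7.0% (5.8–7.4) | 8.7% | 4.0% |
| 0.10 | 9.0% (8.4–9.9) | 10.8% | 4.2% |
| 0.20 | 13.2% (12.0–14.6) | 15.4% | 4.4% |
| 0.30 | 17.8% (15.5–19.6) | 20.2% | 4.5% |
| 0.50 | 26.3% (24.8–28.0) | 29.1% | 4.8% |

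The spread at ρ = 0 is simulation noise.

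**Effectiveness contrast.** For 23 against 23 clinics, with 7 intervention organizations and an assumed 11 to 16 control organizations, the clinic-level rate is about 7–8% at ρ = 0.1, 9–11% at 0.2, 12–14% at 0.3 and 15–20% at 0.5.

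**The case against.** The strongest reply is that this is a condensed article. No sentence says that the arms are tested as 23 independent clinics. The random-effects statement closes an example in the effectiveness section, and the implementation section lists no random effects and gives no degrees of freedom, which could be left to the analysis plan. It is true that the independence claim is an inference. But the article does specify the correlation structure, twice, and both times stops at the clinic. An analysis plan that followed it would carry the omission forward.

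Second, the size is conditional. Only organization-level variation in change matters, the article gives no figure for it, and inflation at ρ = 0.05 is modest. The simulated test is a plain clinic-level t-test, not the adjusted patient-level mixed model, and it ignores the constrained allocation. All of that stands: the percentages illustrate the problem and are not this trial's error rate. Covariate adjustment might lower ρ. The article also describes insurance workflows clinic by clinic, so shared staff and management are a supposition. Against this, the authors considered the correlation serious enough to randomise whole organizations.

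Third, the effectiveness contrast is not randomised, its controls were matched clinic by clinic, and the number of control organizations is unknown. That part is weaker, though the clustering of the intervention clinics in 7 organizations is documented.

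Fourth, saying that clinics are randomised is not strictly false when they are allocated in organization blocks. That is fair. It is a matter of clear wording, secondary to the model.

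**Conclusion.** The concern holds. The stated models stop one level below the randomised unit, and the article itself gives correlation at the missing level as its reason for allocating organizations. For Arm I versus Arm II, a nominal 5% clinic-level test has a true false-positive rate of about 9% if a tenth of the variance in change lies between organizations, 13% at a fifth and 26% at a half. It is harmless only if that share is close to zero. These figures rest on an assumed share, a 3-versus-4 split of organizations and a simplified clinic-level analysis. That only 7 units were randomised, leaving about 5 degrees of freedom for the arm comparison, does not depend on the assumed share. This should be corrected before the outcome analysis.

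**What to change.** In both quantitative analysis sections, make organization the top-level cluster: a random organization intercept and an organization-by-period effect, with clinic nested within organization. Base inference on organizations:

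- **Arm I versus Arm II:** about 5 degrees of freedom.
- **Intervention versus control:** Satterthwaite or Kenward-Roger degrees of freedom, or cluster-robust errors at organization level with a small-sample correction.
- **Fallback:** with only 7 organizations the variance may not be estimated stably, so prespecify a weighted analysis of organization-level changes.

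A randomisation test over the constrained allocation set is a valid alternative, but it may be too coarse. If only 11/12 splits were admissible, the possible size sets give 6 to 28 labelled allocations, so the smallest two-sided p-value would be 2/28 = 0.07 at best. The constraint actually used should be checked first.

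Name organization as the unit of randomisation in the abstract and the Trial design section, and give the number of organizations per arm.

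The cost is analysis wording and one model level. Organization is known for the intervention clinics and should be available for the controls, which were matched on the organization's state. The Trial status section places implementation in the future, so the change can precede any post-implementation outcome. The price is wider intervals and lower power for Arm I versus Arm II, which is the precision that 7 randomised units provide.

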### Effectiveness-implementation hybrid study design

To further study the uptake and use of these health insurance support technologies, we will blend design components of clinical effectiveness and implementation research. Using an “effectiveness-implementation hybrid design,” as described by Curran and collaborators [32], this intervention study will simultaneously assess the effectiveness of (i) health insurance support HIT tools and (ii) the best strategies for implementing the tools in CHCs. We hypothesize that patients seen at CHCs that receive these insurance support HIT tools will have higher rates of continuous insurance coverage and will be more up-to-date on age- and gender-appropriate cancer screening and prevention services, as compared to those seen at CHCs without the tools. We further hypothesize that CHCs that receive enhanced training and facilitation to support tool use will have higher rates of uptake of the tools and better insurance and cancer prevention rates than CHCs that receive the tools without such enhanced training or those without the tools.

Specifically, we will assess the effectiveness and implementation of a suite of health insurance support HIT tools designed to (1) identify and assist in contacting uninsured CHC patients who are eligible for enrollment in Medicaid and (2) encourage re-enrollment of Medicaid-insured patients before coverage gaps occur. The current study builds on our preliminary work by refining and studying the effectiveness of EHR-based health insurance support HIT tools across a larger number of clinics and studying effective methods for implementation of such tools in an adult patient population [30, 33–35].

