This protocol has several limitations. First, a participant site could withdraw from the study; however, the large number (>300) of OCHIN member CHCs could provide substitute sites. Second, as with any study conducted in “real-world” settings, unobserved changes will undoubtedly occur over time in a non-random fashion within the study environments (e.g., community health insurance outreach efforts). We acknowledge that these unexpected occurrences may make it difficult to isolate the effect of the health insurance support HIT tools and the implementation support strategies in this pragmatic trial. To address this, our approach uses both clinic- and individual-level comparisons. Further, the implementation component of this trial is strengthened by the use of a two-arm cluster-randomized design, and the tool effectiveness component uses a propensity score-matched control group of clinics to adjust for temporal trend. Third, while EHR data sources are not developed for research purposes, we have conducted multiple validation studies and have successfully built research datasets in the past [31–69]. Finally, as with most implementation research, there are questions about sustainability. Conducting this work in partnership with OCHIN positions us to sustain the aspects of the insurance support HIT tools proven effective. OCHIN is committed to maintaining the tools and will also enable rapid dissemination to more CHCs.

Despite these limitations, this study has great potential impact, given the central role played by CHCs in providing health care to vulnerable populations and the expansion of both CHCs and public health insurance coverage for adults as supported by the American Recovery and Reinvestment Act and the ACA [70]. Indeed, as health insurance expansions continue, it becomes increasingly important to know about effective methods for connecting patients to coverage. The proposed study will contribute to this knowledge gap. We believe our findings will have broad relevance to public health and healthcare reform efforts. We will work with our community partners and state policymakers to widely distribute findings and plan for widespread dissemination of the insurance support HIT tools, if proven effective. Further, the insurance support HIT tools have the potential to facilitate access to a wide range of recommended healthcare services beyond cancer screening and prevention.

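### Arm I vs Arm II was randomised as 7 organizations, but the analysis described for it names only serial and clinic-level correlation, so its error would be understated

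*Protocol article*

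**What the plan says.** Under Intervention sites, the protocol article reports that "23 clinics in 7 health center organizations agreed to participate" and that "the number of primary care clinic sites per organization ranged from 1 to 6". The unit of allocation and its reason are explicit: "Due to the possible correlation among clinic sites in the same organization, an independent biostatistician randomized the 23 clinics by service organization". The draw was restricted: "A covariate-constrained cluster randomization [44] was used to balance the number of clinics between the two treatment arms". It was also balanced on "state the organization was located in (Oregon vs. non-Oregon), total number of patients per organization, and percentage of uninsured patients per organization". The outcome was 11 clinics in Arm I and 12 in Arm II. No tolerance is given for any of these balance criteria.

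The section on quantitative analysis of the implementation component says that this contrast is handled in a similar way to the effectiveness component, "using DID generalized linear/non-linear mixed models comparing Arm I and Arm II". The effectiveness section, to which it refers, names two sources of correlation to be carried as random effects: serial and within-clinic. Organization is not named in either section.

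The hybrid-design section of the Background states a directional hypothesis for the contrast: "We further hypothesize that CHCs that receive enhanced training and facilitation to support tool use will have higher rates of uptake of the tools", together with better insurance and cancer prevention rates. The Discussion adds that "the implementation component of this trial is strengthened by the use of a two-arm cluster-randomized design".

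**The concern.** The design section and the analysis section point to different units. The design treats the organization as the unit because outcomes may be correlated within it. The analysis, as described, goes down to the clinic and stops there. Arm is constant within an organization, so any organization-level variation feeds directly into the Arm I vs Arm II difference. A model with clinic as its highest level treats 23 clinics as independent when only 7 units were independently allocated. The standard error is then too small and the reference distribution has too many degrees of freedom.

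At stake is the randomised part of the trial. An apparent advantage of enhanced training and facilitation could pass a nominal 5% test much more often than 5% of the time when there is no effect. With so few units and a restricted draw, the randomisation may also offer little room for a small p-value.

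**Working it through.** The article states no sample size, power, alpha or p-value for this contrast, so it has no figure to reproduce. A two-sided 0.05 level is assumed below.

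**Inputs (Intervention sites).** 7 organizations; 23 clinics; sizes from 1 to 6, read here as participating clinics; realised split 11/12. The individual sizes are not given, so every possibility was listed.

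**1. Degrees of freedom.**
- Organization level: 7 − 2 = 5, with critical t = 2.571.
- Clinic level: 23 − 2 = 21, with critical t = 2.080.
- If all variation lies between organizations and the standard error is right, using the 21-df cut-off on a statistic that follows t with 5 df gives a true error of 2·P(t₅ > 2.080) = 0.092.

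**2. Leaving organization out of the model.** Simulation with no arm effect. Each clinic value is an organization effect (variance share ρ) plus a clinic effect (share 1 − ρ). Organizations are allocated to give 11/12 clinics. A two-sample t test on 21 df is applied to the 23 clinic values, and results are averaged over the 19 size sets in step 3. The article gives no ρ, so the values are assumptions.

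| Assumed ρ | True error at nominal 5% |
|---|---|
| 0 | 5% |
| 0.1 | 9% |
| 0.2 | 13% |
| 0.3 | 18% |
| 0.5 | 26% |

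The row ρ = 0 confirms that the test is sound when organizations do not matter.

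**3. What the restricted randomisation can deliver.** Exactly 19 sets of 7 sizes have minimum 1, maximum 6 and sum 23. For each set, all 2⁷ = 128 labelled assignments were checked against the clinic split. Swapping the arm labels leaves a two-sided statistic unchanged, so the smallest attainable p is 2/N, where N is the number of permitted allocations.

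| Splits allowed | N over the 19 sets | Smallest two-sided p | Sets that can reach 0.05 |
|---|---|---|---|
| 11/12 only | 6 to 28 (median 18) | 2/28 = 0.071 to 2/6 = 0.333 | 0 of 19 |
| also 10/13 | 24 to 44 | 2/44 = 0.045 to 2/24 = 0.083 | 7 of 19 |
| also 9/14 | 48 to 60 | 2/60 = 0.033 to 2/48 = 0.042 | 19 of 19 |

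The maximum of 28 occurs for sizes 1, 1, 1, 4, 5, 5, 6. If the sizes 1 and 6 need not both occur among the participating clinics, the 11/12 maximum rises to 36, with p = 2/36 = 0.056. All counts are before the state, patient-number and percent-uninsured criteria, which can only reduce them.

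**The case against.** The strongest reply is that a condensed article leaves degrees-of-freedom methods and small-sample corrections to the analysis plan, and that the mixed-model family it names could hold an organization term. The contrast is called similar to the effectiveness analysis, not identical. This stands in part: silence about a correction is not an error. But the article does more than stay silent. It gives within-organization correlation as the reason for its randomisation, and then lists the correlations to be modelled without that one.

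A reader might infer three stronger things that the text does not support.

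- *That the randomisation cannot give p below 0.07.* The article reports 11/12 as the result and says only that clinic numbers were balanced. It does not say that 11/12 was required, and with a wider tolerance a p below 0.05 is attainable for some or all size sets. Nor does this floor bind the planned model, which is not a permutation test. A model p can be smaller, but it then rests on model assumptions.
- *That the plan uses z-based Wald tests.* No test statistic or reference distribution is named.
- *That the hypothesis or the Discussion sentence is wrong.* The hypothesis sets no significance threshold. The Discussion credits randomisation in the context of non-random changes over time, which is a fair point about confounding.

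**Conclusion.** The point holds as a mismatch between the randomised unit and the correlation structure named for the analysis. If the analysis is carried out as written, the nominal 5% error becomes about 9% to 26% for assumed organization variance shares of 0.1 to 0.5. Using clinic-level degrees of freedom alone gives about 9%, when variation is wholly between organizations and the standard error is otherwise right. The exact size depends on a variance share that the article does not report. The direction does not, as long as the within-organization correlation that the article allows for is positive.

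The permutation floor is conditional: 0.071 to 0.333 only if an 11/12 split was required, lower if wider splits were accepted, and higher again once the other balance criteria are applied. It shows how little the draw may be able to support, and it does not prove that significance is out of reach. The conclusion assumes a two-sided 0.05 level and that the 1-to-6 range describes participating clinics. It concerns only Arm I vs Arm II.

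**What to change.** For Arm I vs Arm II:

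1. Account for organization, either with an organization random effect or by analysing organization-level summaries, and base intervals on t with about 5 degrees of freedom.
2. Add a permutation p over the allocations that met the balance constraints. State how many there were and the smallest p they allow. This needs the constraint tolerances, which should be reported.
3. Interpret the contrast mainly as an estimate with its interval.

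No new data are needed. The Trial status section places randomisation before this article and tool implementation after it, so the analysis could be settled before outcomes were seen. The cost is precision: the critical value alone widens an interval by 2.571/2.080 = 1.24, about 24%, and the organization variance adds more. The claim for the arm comparison will be weaker.
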